**Abstract**

**Background:** Cervical cancer is the leading cause of cancer death in females in Madagascar. In this country, a large-scale screening of precancerous lesions with cytology is hardly possible, because of the lack of specialists and infrastructures. Visual inspection of the cervix with application of 5% acetic acid (VIA) is an inexpensive alternative but very subjective since it depends on the examiner’s experience. Mobile telemedicine is a very promising tool in order to assist non-expert health-care workers in rural area for cervical cancer screening.

**Objective:** To assess if Smartphone may assist health-care worker (on-site) and to evaluate the diagnostic reliability and accuracy of cervical examination with smartphone photos of VIA (D-VIA) compared with conventional VIA, for women testing positive for human papillomavirus (HPV).

**Material and method:** On-site health care workers will be trained in VIA. Prescreened HPV-positive women will be referred to VIA evaluation, during which digital images with a smartphone (D-VIA) will be taken for later evaluation by a VIA specialist in Geneva linked by telemedicine. Women with positive VIA results will be treated with cold coagulation if eligible. Histological results will be considered as gold standard. The results will be analyzed with Cohen’s kappa coefficient, Mcnemar’s test and Bonferroni’s adjustment for multiple comparisons to assess the performance of D-VIA.

**Expected results:** Based on the results of this project, we will develop an educational training and quality assurance program for health providers for VIA and so contribute to a scaling-up of cervical cancer control. An appropriate triage by VIA will reduce not only an excessive referral rate but also an excessive treatment delay, giving the possibility of a “screen (HPV), see (VIA/D-VIA), and treat” program in a single or two visits.

**Key words:** Cervical cancer; HPV; VIA; screening; smartphone; telemedicine

1. **Introduction**

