Primary outcomes:

1) To evaluate if a Smartphone may assist health-care worker (in-site) for cervical cancer screening;

2) To evaluate how the expert at a distant location (off-site) may improve VIA results.

Secondary outcomes:

1) To assess the agreement between diagnoses based on the visualization of the cervix with the unaided eye, after the application of 5% acetic acid (control) during a patient clinical consultation and diagnoses for the same patient based on evaluation of Smartphone photos.

1. **Material and method**

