***Study procedure:***

An informed consent form will be obtained from each woman prior to participation in the study. A questionnaire will then be filled out, assessing socio-demographic data and clinical information. These questionnaires will be available in a secured online platform containing all data from all participants. This platform will be network connected with the University Hospitals of Geneva.

A trained on-site expert will visualize the cervix with a vaginal speculum and then acetic acid 5% will be applied for at least 30 seconds. Then, a conventional VIA is performed.

In addition, acquisition of an additional set of photography of the cervix than that routinely obtained during the exam (with a digital camera or a colposcope) will be performed. The additional digital images will be obtained with a Smartphone (Samsung Galaxy S5). Photographs will be done before and after application of acetic acid and Lugol. This will result in approximately three photos per woman and should yield very little discomfort for the women.

A university-based on-site expert will independently conduct another VIA evaluation, blinded to the health worker’s evaluation.

Biopsies of the cervix (on the four forties and the lesion if any) and endocervical curettage will be performed.

All photographs will be transmitted to University Hospitals of Geneva for expert analysis. This will be made by MMS, e-mail or via RAFT network. All the images will be stored in the online platform.

The “offsite” diagnosis will be transmitted to health care worker having conducted the “in-site” diagnosis and consensus will be discussed.

The on-site health worker and the on-site university-based expert will evaluate the stored digital images (D-VIA) three months after the initial visit, and blinded to their original evaluation.

Since correlation between cytology and histology is known to be poor ([4](#_ENREF_4)), a cervical smear will be done at the end of the procedure.

Subjects deemed to be VIA positive will be treated at the same visit with cold coagulation if eligible (see flowchart).

All photographs stored in the database will be later used for educational purposes.

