***Statistical analysis:***

Sample size: Based on previous studies in Ambanja (population of 28,468), Madagascar, we assume that the prevalence of CIN2+ lesions detected by D-VIA will be of 8% and of 4% by classical VIA interpretation. We have assumed 80% power at an alpha level of 0.05, using a 2-sided hypothesis. With this assumption, 1000 women will be needed.

Adequacy results: VIA and D-VIA results will be categorized as “satisfactory” (positive or negative) and “unsatisfactory”. Adequacy results (satisfactory or unsatisfactory) will be compared. Comparisons of percentages will be made between positive and negative VIA and positive and negative D-VIA. The McNemar’s test for comparisons and the Cohen’s kappa coefficient to measure reproducibility between VIA and D-VIA will be used.

Agreement results: Percentage of agreement will be calculated for each pair of on-site results and for distant D-VIA results by using McNemar’s test and adjust the p values with Bonferroni correction for multiple comparisons in order to overcorrect for Type I errors. Agreement of results will be also evaluated using Cohen’s kappa coefficient.

The following agreement results between assessors will be determined:

1) VIA results made by on-site health worker vs. distant expert D-VIA results

2) VIA results made by on-site expert vs. distant expert D-VIA results

3) VIA results made by on-site health worker vs. VIA results made by on-site expert

4) VIA results made by on-site health worker vs. on-site health worker’s D-VIA blinded results at 3 months

5) VIA results made by on-site expert vs. on-site expert D-VIA blinded results at 3 months

6) On-site health worker’s D-VIA blinded results at 3 months vs. on-site expert D-VIA blinded results at 3 months

7) On-site health worker’s D-VIA blinded results at 3 months vs. distant expert D-VIA results

8) On-site expert D-VIA blinded results at 3 months vs. distant expert D-VIA results

Accuracy: Sensitivities and specificities for the gold standard (cervical histology) will be obtained with the Smartphone diagnosis. Positive and negative predictive values will also be determined.

1. **Expected contribution**

Smartphone high-quality photographic technology has proven to be very useful in detecting pre- cancerous lesions on the cervix in a previous study that also took place in Madagascar.

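### The aim and sample size compare D-VIA with VIA, but accuracy against histology is planned for the smartphone reading only, and no listed analysis tests the hypothesis the study is sized on

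*Protocol*

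**What the plan says.** The comparative intent appears in three places in the protocol:

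- The Abstract states the objective as "to evaluate the diagnostic reliability and accuracy of cervical examination with smartphone photos of VIA (D-VIA) compared with conventional VIA", and adds: "Histological results will be considered as gold standard".
- The Objective section gives as its second primary outcome "To evaluate how the expert at a distant location (off-site) may improve VIA results". Agreement between unaided VIA and the photo reading is listed there as the secondary outcome.
- The sample-size paragraph under Statistical analysis reads "we assume that the prevalence of CIN2+ lesions detected by D-VIA will be of 8% and of 4% by classical VIA interpretation", with 80% power, two-sided alpha 0.05 and 1000 women.

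The analyses listed under Statistical analysis are:

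- **Adequacy:** satisfactory v unsatisfactory results are compared, and "Comparisons of percentages will be made between positive and negative VIA and positive and negative D-VIA", using McNemar's test and Cohen's kappa.
- **Agreement:** McNemar's test with Bonferroni correction, and kappa, for eight pairs of readings.
- **Accuracy:** "Sensitivities and specificities for the gold standard (cervical histology) will be obtained with the Smartphone diagnosis", followed by "Positive and negative predictive values will also be determined", which names no index test.

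On verification, the Study procedure says "Biopsies of the cervix (on the four forties and the lesion if any) and endocervical curettage will be performed", with no restriction by VIA result. In the flowchart the VIA-negative branch also awaits biopsy results.

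**The concern.** A claim that one method is more accurate than another needs both methods measured against the reference standard in the same women, and a test of the difference. The protocol measures only one side. Its paired tests do involve VIA, but they count positives without asking whether disease was present, so a false positive weighs as much as a detected lesion.

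If the plan is followed as written, the report would hold D-VIA accuracy with no comparator, plus paired tests of positivity that say nothing about accuracy. The contrast used to size the study would go untested. The comparison would then have to be chosen after the data are in. With two on-site VIA readings and three D-VIA readings per woman, that leaves considerable room to select.

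**Working it through.** **The plan's own figure.** The sample size rests on a difference d = 0.08 − 0.04 = 0.04 in CIN2+ detected.

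- Two independent proportions, two-sided 0.05, 80% power: 553 per group, 1106 in total.
- Paired McNemar, n = (z_a√ψ + z_b√(ψ − d²))² / d², where ψ is the discordant proportion. If every VIA detection is also a D-VIA detection, ψ = 0.04 and n = 194. If none overlap, ψ = 0.12 and n = 587.

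Neither gives 1000. That is a separate matter, and the present point does not depend on it. What matters here is that the sized quantity is CIN2+ detected, which needs histology for both methods.

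**Can the planned positivity tests stand in for accuracy?** The protocol gives no total CIN2+ prevalence, sensitivity or specificity, so the values below are assumptions. Take 1000 women, of whom 100 have CIN2+ and 900 do not, with readings independent given disease.

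*(a) Same sensitivity, worse specificity.* Sensitivity is 40% for both; specificity is 90% (VIA) and 80% (D-VIA).

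- Positivity: VIA (40 + 90)/1000 = 13%; D-VIA (40 + 180)/1000 = 22%.
- D-VIA positive only: 100(0.4)(0.6) + 900(0.2)(0.9) = 24 + 162 = 186.
- VIA positive only: 100(0.4)(0.6) + 900(0.1)(0.8) = 24 + 72 = 96.
- z = (186 − 96)/√(186 + 96) = 90/√282 = 5.36, p about 8 × 10⁻⁸.

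The test is highly significant although detection has not improved and specificity is worse. With 80 CIN2+ cases, z = 92/√277.6 = 5.52; with 200 cases, z = 80/√304 = 4.59. The difference of 90 is fixed by the margins. If the two readings are positively correlated given disease, only the discordant total shrinks, so z rises.

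*(b) Doubled sensitivity, no signal.* D-VIA has sensitivity 80% and specificity 90%; VIA has 40% and 85.6%.

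- D-VIA positives: 80 + 90 = 170. VIA positives: 40 + 130 = 170, since 1 − 130/900 = 85.6%.
- Positivity is 17% for both. The expected McNemar difference is zero, whatever the dependence between readings.

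*(c) The protocol's 4% and 8%, used here as positivity.* Let VIA have 30 true and 10 false positives (sensitivity 30%, specificity 890/900 = 98.9%). D-VIA has 80 positives in each row:

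| D-VIA true / false positives | Sensitivity | Specificity | Against VIA |
|---|---|---|---|
| 70 / 10 | 70% | 98.9% | better |
| 30 / 50 | 30% | 94.4% | worse |
| 20 / 60 | 20% | 93.3% | worse on both |

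All three rows can give the same discordant counts, 50 v 10, and so the same McNemar result: (50 − 10)²/60 = 26.7, exact p = 1.6 × 10⁻⁷. The test cannot tell the rows apart.

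**Would the missing comparison have power?** Read 8% and 4% as true detections, 80 v 40 among 1000 women, and assume 80 to 200 CIN2+ cases. Sensitivities are then 100% v 50% (80 cases), 80% v 40% (100), 53% v 27% (150) and 40% v 20% (200). The paired formula above, applied within CIN2+ women at two-sided 0.05, needs between 14 and 116 cases, depending on case number and overlap. Power with the assumed cases is at least 96%. Power for specificity cannot be computed, because the protocol gives no false-positive rate.

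**The case against.** Several points on the other side have weight.

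- *The McNemar and kappa analyses fit their labels.* They sit under adequacy and agreement, and agreement is a stated secondary outcome. The protocol nowhere says that more positives means better accuracy. This stands: the fault is that nothing else carries the comparative question. In example (a) the planned D-VIA specificity of 80% and predictive value of 40/220 = 18% would expose over-calling, but with no VIA figure beside them.
- *A reader might infer that no primary outcome has any analysis.* The document does not support that. Pairs 1 and 2 set each on-site VIA reader against the distant expert, which bears on the second primary outcome, and D-VIA accuracy bears on the first. For improvement, however, agreement is not enough.
- *A reader might infer that the study cannot answer the question.* That is also too strong. The readings and histology are planned in the same women, so the limit lies in the stated analyses, not the data.
- *The sample-size sentence may imply relative detection, and a separate analysis plan may spell it out.* The first is a fair reading, but no listed analysis takes it up, and it would not cover specificity. As to the second, the protocol does not leave accuracy open: it states that analysis and names only the smartphone diagnosis. Interval methods and the handling of unsatisfactory readings can be left to an analysis plan; the comparison itself is the stated objective.
- *The numbers are assumed.* They are. They show what can happen, not what is expected.

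**Conclusion.** The point holds for the plan as written. The objective and the sample size are comparative against histology, the accuracy analysis covers one method, and the paired tests ignore histology. The listed analyses therefore cannot show which method is more accurate, and none tests 8% v 4% CIN2+ detected.

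That conclusion comes from setting the protocol's own sections side by side and needs no assumed figure. The sizes (z of 4.6 to 5.5 with no gain in detection, and a zero expected difference with sensitivity doubled) are illustrations under assumed prevalence, sensitivity and specificity. The z values also assume conditional independence.

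Two further inferences should be avoided. A difference between health-worker VIA and distant D-VIA could not be credited to the smartphone, because reader and modality change together. Nor can the teleconsultation consensus be assumed available for analysis: the protocol says it will be discussed, not that it is recorded as a study variable.

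**What to change.** Amend the Accuracy paragraph under Statistical analysis as follows.

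1. Define disease as histological CIN2+, the threshold already used for the sample size. Give sensitivity, specificity, PPV and NPV with 95% confidence intervals for health-worker VIA, on-site expert VIA and each D-VIA reading.
2. Name as primary the paired difference in CIN2+ detection between VIA and distant-expert D-VIA (McNemar within CIN2+ women), and say which on-site VIA reading is meant. Report the paired specificity difference (McNemar within women without CIN2+) beside it.
3. State that health-worker VIA v distant D-VIA reflects reader and modality together. Analyse the same-reader pairs 4 and 5 in the same way to isolate modality.
4. Analyse the consensus diagnosis in this way only if it is recorded as a study variable.
5. Keep the existing McNemar and kappa analyses for adequacy and agreement.

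The cost of items 1 to 3 and 5 is wording and a few extra tables, since the VIA readings, D-VIA readings and histology are already planned in the same women. Item 4 may need an added data field.

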**5.1 Flowchart**

Learning and improvement of VIA interpretation over time

(Photos used for education purposes)

**Management according to WHO guidelines**

Treat for cancer

Post-treatment Follow-up

**Treat**

Not eligible for cold coagulation

**VIA +**

eligible for cold coagulation

CANCER

CIN

Conisation

**Wait biopsy results**

**Recall**

CIN or Cancer

**VIA -**

**Wait biopsy results**

Negative

Repeat VIA in 5 years

Repeat VIA in 1 year

Negative

VIA + Biopsy

Quality control

**E-mail**

**MMS**

**HPV positive Women 30-69 years**

Followed by directed & 4-quadrant biopsies & endocervical brushing

By on-site health worker

By on-site expert

**DATA BASE (Online Platform)**

For D-VIA evaluation

Distant expert

By on-site health-worker (at 3 months)

By on-site expert (at 3 months)

**Off site diagnosis**

**On site diagnosis**

**TELECONSULTATION**

**DIAGNOSIS CONSENSUS AND MANAGEMENT**
